## Materials and methods

Design

A quasi-experimental cluster study with intervention and control arms is being conducted between July 2024 and July 2026 [23,24]. The evaluation will be pre-post intervention assessments following the type 1 implementation-effectiveness hybrid design [23]. The quantitative component of the study aims to estimate changes in effectiveness indicators, and the qualitative component will explore the context of implementation and community acceptance.

Settings

This study is being conducted in the Sepone and Vilabuly districts in southern Lao PDR as part of the evaluation of the Japanese International Cooperation Agency (JICA) Grassroot Project entitled "Project for Improvement of MCH by Enhancing Women's Empowerment in Poor and Remote Areas in Sepone District." The two districts are located in Savannakhet Province, approximately 600 kilometers from Vientiane, the capital city of Lao PDR, and close to the Vietnam border [25]. The map of study sites in Lao PDR is shown in Appendix A.

Sepone and Vilabuly share similarities, as both are mountainous areas with ethnic groups, including Lao-Tai, Phutai, Tri, and Makong, and poverty rates of 44.0% and 40.8%, respectively, as of 2018 [25-27]. According to the Savannakhet Health Provincial Office, Sepone and Vilabuly each have a district hospital, with 14 health centers in Sepone and 12 in Vilabuly [28].

Out of the 88 villages in Sepone, 19 intervention sites were selected in the catchment areas of five health facilities. These sites are called "model villages," as they previously implemented the 2017-2019 phase of the JICA Grassroot Project to promote ANC and facility-based delivery [29]. Since the project aims to extend the pairing of female and male VHVs/VHWs to all villages of Sepone District by 2024, we selected 18 control sites in the catchment areas of five health facilities of Vilabuly out of its 73 villages. The list of intervention and control villages in Sepone District and Vilabuly District is presented in Appendix B.

Participants

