The target population of the quantitative component of the study is women aged 15-49 years who reside at the study sites. The participants will be women who gave birth within 12 months at the time of both the baseline and endline surveys. Women whose births resulted in stillbirths, those who did not consent to participate in the surveys, or those who faced a language barrier with surveyors - due to the presence of ethnic minorities who speak different local languages - will not be enrolled. In contrast, the qualitative component targets additional groups, such as village health volunteers and workers, male partners, family members, and health center staff.

Sample size and sampling method

We estimated the sample size using the logistic regression formula n > 10 m, where the minimum "n" of respondents with or without the study outcome is 10 times the number of covariates "m" to be included in the regression [30]. We estimated at least 80 facility-based follow-up PNC users with eight potential covariates. In 2022, VHVs/VHWs reported that there were 302 children of ≤1 year of age in the 37 targeted villages, including 137 from the 19 villages in Sepone and 165 from the 18 villages in Vilabuly. Due to the relatively low yearly delivery at the target sites, we will conduct exhaustive sampling at the baseline to include all eligible subjects, ensuring representative results [31].

For the end-line survey, we estimated the required sample size for difference-in-differences analyses to assess changes in the primary outcome before and after the intervention. We anticipate a 15.0% increase in facility-based follow-up PNC in the intervention villages and a 5.0% increase in the control villages over two years of implementation. Using a two-tailed z test for the difference between proportions, with 80% statistical power at the 5% significance level, unequal cluster size assessment, a design effect of 2, and a non-response rate of 10%, we estimated a sample size of 302 for the end-line survey [32,33].

Finally, at least 12 participants will be selected purposively for interviews in the qualitative component [34]. The enrollment of further participants will depend on when data saturation is reached.

Intervention, monitoring, and assessments

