Qualitative data will be gathered through key informant interviews and focus group discussions (FGDs). Interview and FGD guides will be developed in Lao, and interviewers (medical students) will receive training in qualitative data collection techniques. With participants’ consent, all interviews and discussions will be audio recorded, anonymized, and securely stored on a drive accessible only to the research team. The qualitative study will be conducted during the implementation phase to examine how the intervention is delivered and perceived, and to gain insights into the processes influencing its effectiveness. Interview and discussion guides will focus on the dynamics of interactions between VHVs/VHWs and mothers, between VHVs and mothers’ family members, and among VHVs who work together.

Data analysis

We will conduct difference-in-differences analyses using estimated levels of key indicators before and after the intervention, and test the significance of changes in outcomes. Pearson chi-square tests or t-tests will be used, as appropriate, to compare gaps in service use based on women's characteristics and other covariates. For multivariate analyses, mixed-effects logistic regression will be used to evaluate the associations between the primary outcome and predictor variables, while including interaction terms between time and group to assess the intervention effect. Statistics will be reported along with their 95% confidence intervals. P values of <0.05 will be considered to indicate statistical significance. All analyses will be performed using Stata Statistical Software (release 17, 2021, StataCorp, College Station, TX).

For the qualitative component, interview and FGD audio recordings will be transcribed, translated into English, and analyzed using both inductive and deductive content analysis approaches. Relevant codes will be extracted and organized into themes and sub-themes to provide insights into the intervention’s implementation context, feasibility, and acceptance within the community.

Ethical considerations

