## Results

At the end of the study, several outcomes are anticipated in line with the study objectives. First, assuming baseline utilization is about 5% in both districts, we expect a 15% increase in Sepone (intervention) and a 5% increase in Vilabuly (control), resulting in a 10% difference in the proportion of women receiving at least one facility-based follow-up PNC visit. Second, guided by the theory of change, we hypothesize this improvement to result from enhanced counseling and more frequent interactions between mothers, male partners, and VHVs/VHWs through a gender-norms-sensitive approach. Specifically, regular household visits by paired VHVs/VHWs are expected to strengthen trust and satisfaction among mothers and promote male partner involvement, thereby contributing to increased PNC service uptake. Lastly, we also anticipate a longer average duration of postpartum facility stays among mothers in intervention areas.

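### The hypothesis and end-line sample size are a 10-point difference in proportions, but the only covariate-adjusted test of the intervention effect is a ratio of odds ratios, and neither analysis is named as decisive

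*Protocol article*

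**What the plan says.** **Hypothesis.** The Results section works from a common starting level ("assuming baseline utilization is about 5% in both districts") and expects rises of 15 and 5 points, "resulting in a 10% difference in the proportion of women receiving at least one facility-based follow-up PNC visit". This is an additive effect.

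**Sizing.** Under Sample size and sampling method, the end-line survey is sized for DiD analyses: "We anticipate a 15.0% increase in facility-based follow-up PNC in the intervention villages and a 5.0% increase in the control villages". The calculation is also on the additive scale: "Using a two-tailed z test for the difference between proportions", "with 80% statistical power at the 5% significance level", with a design effect of 2 and 10% non-response.

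**Analysis.** The Data analysis section plans two routes to the effect on the primary outcome. The first is on levels: "We will conduct difference-in-differences analyses using estimated levels of key indicators before and after the intervention", with a significance test. The second is a mixed-effects logistic regression on predictor variables, "including interaction terms between time and group to assess the intervention effect". The Abstract gives the same order and describes the logistic model as the one adjusted for covariates and time effects. Both fall under the same 0.05 threshold. Nothing says which takes precedence, or that the logistic result will be turned into a difference in proportions.

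**Sites.** The Settings section says the intervention villages were chosen "as they previously implemented the 2017-2019 phase of the JICA Grassroot Project to promote ANC and facility-based delivery". The controls are in another district.

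**The concern.** The time-by-group coefficient in a logistic model is the log of a ratio of odds ratios. That is a different estimand from a difference between two changes in proportions, and it has a different standard error.

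This matters because the article itself concedes possible selection bias and confounding. In a non-randomised comparison of two districts, readers will lean on the adjusted result, and that result is not on the scale of the hypothesis or of the sample size. Three things are at stake:

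- whether the adjusted analysis answers the stated question;
- how likely it is to detect the hypothesised effect;
- what is concluded if the two analyses differ, when the choice between them would be made after seeing the data.

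**Working it through.** **Inputs from the article.** Baseline 5% in both districts; rises of 15 and 5 points, so 20% and 10% at end-line. Births per wave are taken from the 2022 counts: 137 (Sepone) and 165 (Vilabuly). Two-sided 5% level; design effect 2.

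**1. The scale of the sample size.** Two-proportion z test, unpooled variance, 15% versus 5%:

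(1.960 + 0.842)² × (0.15×0.85 + 0.05×0.95) / 0.10² = 137.4

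137.4 × 2 (design effect) = 274.7; × 1.1 (non-response) = 302.2.

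This reproduces the stated 302 and confirms that the sizing is additive. It does so as a number per arm and with 15% and 5% as the compared proportions. That is a separate matter and is not relied on here.

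**2. The interaction at the article's own rates.** With odds(p) = p/(1−p):

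- intervention: odds(0.20)/odds(0.05) = 4.75
- control: odds(0.10)/odds(0.05) = 2.11
- ratio of odds ratios = 4.75 / 2.11 = 2.25; log = 0.811

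**3. Power of each test on the same data** (Wald approximation, unadjusted).

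Logistic interaction: variance = Σ 1/[n p(1−p)] over the four cells = 0.154 + 0.046 + 0.128 + 0.067 = 0.394, so SE = 0.628.

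Additive DiD: variance = Σ p(1−p)/n = 0.000347 + 0.001168 + 0.000288 + 0.000545 = 0.00235, so SE = 0.0485.

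Power = Φ(effect/SE − 1.96). A design effect of 2 multiplies each SE by √2.

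| Design effect | Interaction: effect/SE | Power | Additive DiD: effect/SE | Power |
|---|---|---|---|---|
| 1 | 0.811/0.628 = 1.29 | 25% | 0.10/0.0485 = 2.06 | 54% |
| 2 | 0.811/0.888 = 0.91 | 15% | 0.10/0.0685 = 1.46 | 31% |

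If 302 women *per arm* were surveyed at end-line (baseline still 137 and 165), the figures would be 28% versus 74% and 16% versus 46%. The gap does not close.

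**4. Unequal baselines.** The article gives no separate baselines for the two arms, so the unequal ones below are assumptions. The rises of 15 and 5 points are kept, so the additive effect is 10 points in every row.

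| Intervention | Control | Ratio of odds ratios |
|---|---|---|
| 5% to 20% | 5% to 10% | 2.25 (article's assumption) |
| 10% to 25% | 5% to 10% | 3.00/2.11 = 1.42 |
| 10% to 25% | 3% to 8% | 3.00/2.81 = 1.07 |
| 20% to 35% | 5% to 10% | 2.15/2.11 = 1.02 |

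In the reverse case, with no additive effect (15% to 20% versus 5% to 10%), the ratio is 1.42/2.11 = 0.67.

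**The case against.** **The additive DiD is already planned.** It comes first, the end-line survey is sized for it, and the Abstract presents the regression as a later step that assesses an association. This is fair, and it means the plan does not miss its hypothesis. It does not settle the matter: the DiD is described without covariates, while the adjusted model is expressly given the task of assessing the intervention effect.

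**The divergence is hypothetical.** A reader might infer that the interaction will be near 1 even when the hypothesised effect is fully present. The documents do not support that. At the assumed 5% in both districts the ratio is 2.25, and for any equal baselines it stays at about 1.5 or more. Values near 1 need an imbalance that the article does not assume. The earlier project promoted antenatal care and facility delivery, not follow-up PNC, and the Introduction puts additional PNC visits below 5% in 2017. An imbalance is possible but undocumented.

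**Harm.** A reader might also infer that the model would show harm when the 10-point gain occurred. No row in the table does so. With control at 5%, the ratio reaches 1.00 only at an intervention baseline of 21.1%. It falls below 1 sooner only if the control level is assumed lower still (0.93 at 8% versus 2%). The 0.67 belongs to a scenario with no additive effect.

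**The two scales need not disagree.** Every row of the table points the same way on both scales, three of them with unequal baselines. If control use is flat, the signs always agree. Divergence needs unequal baselines together with a time trend, although the article does anticipate a 5-point control rise.

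**Both analyses are underpowered.** This is true, and sample size is the larger problem. The relative loss from the choice of scale is still real.

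**Effect-measure detail may sit in a fuller document.** That is possible. But the article itself names the interaction as the assessment of the effect, on a scale that differs from its own hypothesis.

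**Conclusion.** The point holds in this form: the hypothesis and sizing are additive, the only covariate-adjusted test of the intervention effect is multiplicative, and precedence is not stated.

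The cost that needs no assumption about imbalance is power. At the article's own rates the interaction has roughly half the power of the additive DiD (25% versus 54%; 15% versus 31% with a design effect of 2). Possible divergence between the two analyses is a further risk, conditional on unequal baselines and a rising control level.

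The power figures are rough. They are unadjusted Wald approximations resting on about 7 and 8 expected baseline users per arm (0.05 × 137 = 6.9; 0.05 × 165 = 8.3). The ratios are marginal; a village random effect would move the conditional ratio somewhat away from 1. Neither caveat alters the mismatch of scale. The change should be made, because choosing between the two results after the end-line data are known would be a data-dependent choice.

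**What to change.** Before the end-line survey planned for around July 2026, add a statement to the Data analysis section that:

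- the decisive analysis of the primary outcome is the covariate-adjusted risk-difference DiD, with a 95% CI that allows for clustering by village;
- it is obtained as the group-by-time contrast of predicted probabilities from the planned mixed-effects logistic model (Stata's margins command); an identity-link model with group, time, their interaction and village-clustered standard errors is an acceptable alternative, but one of the two should be fixed in advance;
- the interaction odds ratio is reported as secondary, with no separate claim of effectiveness.

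The cost is about one sentence of text. The data, the software and the fitted model can stay as planned. The change does not cure the low power of the additive analysis, which is a question of sample size.

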## Results

At the end of the study, several outcomes are anticipated in line with the study objectives. First, assuming baseline utilization is about 5% in both districts, we expect a 15% increase in Sepone (intervention) and a 5% increase in Vilabuly (control), resulting in a 10% difference in the proportion of women receiving at least one facility-based follow-up PNC visit. Second, guided by the theory of change, we hypothesize this improvement to result from enhanced counseling and more frequent interactions between mothers, male partners, and VHVs/VHWs through a gender-norms-sensitive approach. Specifically, regular household visits by paired VHVs/VHWs are expected to strengthen trust and satisfaction among mothers and promote male partner involvement, thereby contributing to increased PNC service uptake. Lastly, we also anticipate a longer average duration of postpartum facility stays among mothers in intervention areas.

## Discussion

In ethnic minority communities with strong patriarchal norms, women often face restrictions that limit their interactions with male CHWs, especially on sensitive topics like reproductive and maternal health [37-39]. In such settings, female CHWs are often preferred, as women are generally seen as mainly responsible for childcare [37]. Likewise, cultural norms may prevent CHWs, particularly females, from interacting with men outside their families, limiting communication with male household heads who play a key role in healthcare decisions [37]. Pairing male and female CHWs can help overcome these challenges by enabling more culturally appropriate communication. In Lao communities, this is important, as most VHVs/VHWs are men due to higher literacy rates, but are often less accepted when engaging directly with women on sensitive health issues. Male CHWs can focus on engaging male partners and handling literacy-based tasks like reporting, while female CHWs support mothers through counseling and education. This approach may strengthen both maternal care and male involvement in ways that respect local culture. 

Therefore, the present quasi-experimental study aims to estimate the effectiveness of female and male VHVs/VHWs working as pairs in increasing the uptake of facility-based follow-up PNC services among ethnic minorities in the Lao PDR.

Strengths and limitations

The study has several strengths. To our knowledge, it is the first in the Lao PDR to assess the effectiveness of a community-based intervention involving CHWs to improve continuity of care between health facilities and mothers, while addressing barriers related to gender norms. The pairing of male and female CHWs in this intervention aligns with the Lao National Primary Health Care Policy’s goal of rethinking strategies for delivering primary healthcare through VHVs/VHWs [15]. Moreover, implementing the intervention in collaboration with the Savannakhet Health Provincial Office increases the likelihood of local ownership, while the selection of sites ensures that the study recommendations are relevant to many other settings in Lao PDR, where VHVs/VHWs are predominantly male [8,9].

Despite its strengths, this study has a few potential limitations. First, the choice of a quasi-experimental design was made due to feasibility constraints; however, the lack of randomization increases the risk of selection bias, where systematic differences between groups may impact the results. Efforts were made to select target sites with sociodemographic and cultural similarities to minimize these differences, yet confounding factors such as varying healthcare access may still affect the outcomes. Second, as key factors will be assessed through self-reports, this may introduce reporting biases. Nonetheless, the validation of service utilization will be confirmed through mothers' medical handbooks.

## Conclusions

The Lao PDR has committed to expanding access to MCH services by promoting collaboration between male and female VHVs/VHWs. However, the extent to which this strategy can reduce gender norm-related barriers, particularly in ethnic minority communities, remains uncertain. This study aims to provide evidence to support the government’s approach by assessing the effectiveness of pairing male and female CHWs in improving key outcomes, including the uptake of facility-based follow-up postpartum care. In addition, it will document lessons learned from the intervention’s implementation to inform future scale-up.

